Gait, strength and balance will be assessed with five tests of which the three first are recommended as part of the STEADI initiative of the Centers for Disease Control and Prevention (CDC) [65]:The “Timed Up and Go” test (TUG) [66–68] assesses lower extremity function, mobility and fall risk. It is not only associated with motor performance but also with cognitive function [69]. It is associated with history of past falls, but its predictive ability for future falls is limited [70] so it may be used in combination with other tests in fall risk assessment [71]. Patients sit on a chair and on the command “Go”, they have to stand up, walk three meters at a comfortable and sage pace, turn, walk back to the chair and sit down. The time is measured in seconds, begins at “Go” and ends when the patient is seated. The patients will perform the task twice. The average of both scores will be used in the analysis.The “Four-Test balance scale” [72], also called “Four Stage Balance Test” (FSBT) by the CDC, consist of standing in four progressively more difficult stances: 1. Feet side-by-side; 2. Partial tandem; 3. Tandem and 4. On one foot. If the patient can hold a position for ten seconds without moving his/her feet or needing support, he/she goes on the next position. If not, the test is stopped. The level reached will be noted.The “Five Time Sit to Stand” test (FTSTS) was described to test the ability to rise from a chair in a short battery of physical-performance tests [73]. It is a valid measure of dynamic balance and functional mobility in older adults and has excellent relative and absolute reliability and reproducibility [74]. With a cut-off value at 12 s it demonstrates a reasonable sensitivity and specificity in identification of multiple fallers [75]. Patients sit on a straight-backed chair placed next to a wall; they will be asked to fold their arms across their chest and to stand up five times in a row as quickly as possible, when the assessor says “Go”. Patients have to come to a full standing position each time they stand up and have to sit down without touching the back of the chair. The time is measured in seconds, begins at “Go” and ends with the fifth seat. The patients will perform the task twice. The average of both scores will be used in the analysis.The “Functional Reach” test (FR) [76–78] was designed to identify frail older people and elders at risk of falling. It measures the maximal distance that a person can reach forward while standing. The patient will stand next to a wall with the ipsilatéral arm at 90° flexion with fingers extended. The assessor will mark a point where the third finger is at the initial position on a static squared paper against the wall. The command is “*Lean forwards as fare you can without taking a step, bending the knee or raising the heels to bring your hand forward as far as possible*”. At the maximal anterior leaning position, the assessor marks a second point. The horizontal distance between the two points will be measured in centimetres. The patients will perform the task three times. The average of the three scores will be used in the analysis.The “Six-meter-walk” test (SMWT) will be used to assess gait speed. Patients will walk “*as fast as possible without running*” ten meters including 2-m approach, 6-m for the time measure and 2-m beyond the measure to ensure a constant walking speed across six meters [79–81]. The time will be measured in seconds and divided by 6 to calculate the gait speed in m/s. The patients will perform the task twice. The average of both measures will be used in the analysis.

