### Statistical analysis

Descriptive statistics will be used to present group characteristics on age, sex, body mass index, base of support width (BSW) [86, 87], and history of falls, activity of daily live, physical activity habits, and risk factors for falls.

According to statistical criteria of termination of the trial, we have no predefined stopping rules because we are not expecting risks that are different in the groups (i.e. no adverse event stopping criteria).

We will use an intention-to-treat analysis based on all randomized patients, with missing values and dropouts replaced by multiple imputation methods, as recommended by current guidelines on randomized controlled trials [88].

The primary analysis will be done to test for the incidence of falls. We follow the proposition of Röhmel and Pigeot [89], who showed that superiority of the experimental group (“T&E” in our case) over the reference treatment (“Otago” in our case) can be tested after successfully demonstrating non-inferiority (if stated a-priori in the protocol). To simultaneously demonstrate superiority of E (T&E) to R (Otago) and R (Otago) to P(Helsana) as well as the non-inferiority of E (T&E) to R (Otago), we will use negative binomial regression [90, 91] and follow an approach proposed by Mütze et al. [84]. A sensitivity analysis without multiple imputations of missing values will be performed.

For the primary analyses, we will adjust for the participants’ length of observation, center, age and risk for falls category [92]. We will perform a per protocol sensitivity analysis including time varying co-variables to reduce confounding and selection bias, e.g. due to differential censoring.

Further analyses will be performed to test the secondary endpoints quality of life (Overall score of OPQOL-35), severity of falls (Schwenk Scale), fear of falling (FES-I), functional capacities (TUG, FSBT, FTSTS, FR and SMWT), as well as adherence to the exercise recommendations (duration in min/week, frequencies/week).

We will perform a subgroup analysis based on age groups to test the secondary hypothesis that compliance in older group is better with the Otago compared to T&E and that in younger participants’ compliance is better in T&E compared to Otago.

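### The six-metre walk rule contradicts its own unit: time divided by 6 is pace in s/m, not gait speed in m/s

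*Protocol article*

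**What the plan says.** In the Outcomes section of the protocol article, the six-metre walk is the last of the five tests of gait, strength and balance. Its purpose is plain: the "test (SMWT) will be used to assess gait speed". The course is "ten meters including 2-m approach, 6-m for the time measure and 2-m beyond the measure to ensure a constant walking speed across six meters", so the timed distance is 6 m. The derivation follows: "The time will be measured in seconds and divided by 6 to calculate the gait speed in m/s". The walk is done twice, and "The average of both measures will be used in the analysis".

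The Statistical analysis section names the test among the secondary endpoints, under "functional capacities (TUG, FSBT, FTSTS, FR and SMWT". No other part of the article restates the formula or says which direction of the score is better.

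**The concern.** Speed is distance over time. The sentence gives time over distance and attaches the unit of speed. The two quantities are reciprocals, so they rank walkers in opposite order and agree at one value only.

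An analyst who codes the sentence as it stands, or a reader who trusts the m/s label, would take a higher value as better. A group that walks faster after the programme would then generally look slower. A plausibility check on the range would not reveal this, because both quantities fall in a similar numerical range for ordinary walking times.

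**Working it through.** **Inputs from the article (Outcomes).** Timed distance 6 m; time t in seconds; stated rule t/6; stated unit m/s; average of two trials analysed.

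**Inputs assumed.** The article gives no walk times. All times below are illustrations and show how the formulas behave, not what this trial will observe.

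**Step 1: units.** As written: t seconds / 6 metres = t/6 s/m. Speed: 6 metres / t seconds = 6/t m/s. The stated unit is not reproduced by the stated rule. The two are equal only when t² = 36, that is t = 6 s.

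**Step 2: single values (assumed times).**

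| Time (s) | As written, t/6 | Speed, 6/t (m/s) |
|---|---|---|
| 3 | 0.50 | 2.00 |
| 4 | 0.67 | 1.50 |
| 5 | 0.83 | 1.20 |
| 6 | 1.00 | 1.00 |
| 8 | 1.33 | 0.75 |
| 10 | 1.67 | 0.60 |
| 12 | 2.00 | 0.50 |

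From 3 to 12 s both columns run over the same range, 0.50 to 2.00, in opposite order.

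**Step 3: changes (assumed times).**

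- 7.5 s to 5.0 s: correct 6/5.0 - 6/7.5 = 1.20 - 0.80 = +0.40 m/s; as written 5.0/6 - 7.5/6 = 0.83 - 1.25 = -0.42.
- 5.0 s to 4.5 s: correct +0.133 m/s; as written -0.083.
- 8 s to 7 s: correct +0.107 m/s; as written -0.167.

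The size changes as well as the sign, and not by a constant factor, so reversing the sign afterwards does not recover m/s.

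**Step 4: group means.** With simulated lognormal times (assumed median 5.5 s, SD 0.25 on the log scale) and every time shortened by 10%, the difference in means is +0.125 m/s correctly and -0.095 as written.

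**Step 5: does the sign always reverse?** No. Take assumed times of 4 and 10 s in one group and 6 and 7 s in the other.

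- As written: (4 + 10)/2/6 = 1.167 against (6 + 7)/2/6 = 1.083.
- Correct: (1.50 + 0.60)/2 = 1.050 against (1.000 + 0.857)/2 = 0.929 m/s.

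The first group is higher under both formulas, because its times are much more spread out and the reciprocal is non-linear.

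**Step 6: averaging two trials.** For assumed trials of 5 and 7 s, the mean of the two speeds is (1.200 + 0.857)/2 = 1.029 m/s. The speed from the mean time is 6/6 = 1.000 m/s. Under t/6 the order of averaging makes no difference; under 6/t it does.

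**The case against.** The strongest reply is that this is a slip of wording in a condensed article. The construct (gait speed), the distance (6 m) and the unit (m/s) all point to 6/t, and only the words about dividing conflict with them. That may well be so. It does not remove the point, since the derivation is stated and is stated wrongly.

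A second reply is that t/6 is walking time on another scale. A comparison of group means on t/6 gives the same test statistic and p-value as one on raw seconds, and the article analyses two other tests in the same battery (TUG and FTSTS) as times. This also stands: the evidence on walking is not lost. What is wrong is the unit, the direction implied by the label, and any effect size reported in m/s.

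Two stronger readings are tempting. A reader might infer that every treatment effect on this endpoint changes sign. Step 5 shows otherwise: reversal is what an ordinary shift in walking times produces, but it is not guaranteed when the spreads differ greatly. A reader might also infer that the trial's data are already miscalculated. The article says data are entered in REDCap, but describes no derived gait-speed field and does not show which formula is in use.

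**Conclusion.** The rule is wrong as written, because it yields s/m and calls it m/s. That follows from the units alone and needs no assumption. The consequence is conditional: if t/6 is computed, labelled m/s and read with higher as better, slower walkers score higher and an ordinary gain in walking time generally appears as a loss. The figures for the size of the distortion rest on assumed walk times.

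The scope is narrow. One of several secondary endpoints is affected. Falls incidence, its negative binomial analysis, the non-inferiority and superiority tests and the sample size do not depend on it. The point should be fixed before the secondary analyses are run, but it does not threaten the trial's main conclusion.

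**What to change.** Replace the sentence with: gait speed (m/s) = 6 / time in seconds. Add whether speed is computed for each of the two trials and then averaged, or computed once from the mean time. The present averaging sentence fits either reading, and the two differ slightly. State that higher values mean faster walking.

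Then check that any derived variable in REDCap or in the analysis code uses this formula, and recompute from the recorded times where they are stored. The article says that time is measured, not that each trial's time is kept apart from the calculated value, so this needs confirming. If only the averaged t/6 was kept, its inverse gives the speed from the mean time exactly, but not the mean of the two speeds.

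The cost is a short change to the text, a check of one formula and, if needed, one recalculation. No new data have to be collected if the times are stored.

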### Patient flow

Figure 2 describes the patient flow. This trial will last 36 months, and individual patient participation is planned for twelve months. Patients will be recruited from autumn 2016 until autumn 2019. We expect to enrol 20–21 subjects in each of the four regions every six months to reach the sample size. The last follow-up phase should end in autumn 2020.

**Fig. 2 Fig2:**
[figure not shown]
Patient Flow. FES-I: Falls Efficacy Scale - International; MMSE: Mini Mental State Examination; OPQOL-3: Older People’s Quality of Life Questionnaire; TUG: Timed Up and Go test; FR: Functional Reach Test; FSBT: Four Stage Balance Test; FTSTS: Five Times Site To Stand test; SMWT: Six Meters Walk Test; BSW: Base of Support Width

### Data management

All data will be directly entered in REDCap software. This software allows the protection of the confidentiality of the data during the study. As soon a patient gives his written consent he will receive an Identity Code (ID). The project-assistant will verify all data entries before validation. If data are missed, she will ask for complement. For data cleaning, statisticians will be blinded to group allocation. At the end of the study, all the data will be anonymised. The final trial dataset will be accessible to the Data monitoring committee for the analysis. 

### Sample size

To achieve our study objectives, the sample size calculation estimates 405 participants. With a significance level set at 5% (i.e. overall type-I error probability) and power of 80%, an assumed rate of falls of 0.5 for the T&E program, 0.79 for the OTAGO and 0.92 for the usual care group, a non-inferiority margin of 5% and an assumed dropout rate of 15%, we would need to include 162 participants in the groups A and B each, and 81 participants in the group C. We used the R package “ThreeArmedTrials” to calculate the sample size [83].

The allocation scheme of 2:2:1 is based on ethical and statistical considerations, following the recommendations of Mütze et al. [84] and Mielke et al. [85].

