## Abstract

**Background:**

Fall prevention interventions with home-based exercise programmes are effective to reduce the number and the rate of falls, by reducing risk factors. They improve balance, strength, function, physical activity, but it is known that older adults’ exercise adherence declines over time. However, it is unclear which delivery-modalities of the home-based exercise programmes show the best adherence and the largest effect.

We created a new home-based exercise programme, the Test-and-Exercise (T&E) programme, based on the concepts of self-efficacy and empowerment. Patients learn to build their own exercise programme with a mobile application, a brochure and cards, as well as with eight coaching sessions by physiotherapists.

The main objective of this study is to compare the T&E programme with the Otago Exercise Programme and the recommendation-booklet and exercise-cards of Helsana regarding incidence of falls. Other outcomes are severity of falls, functional capacities, quality of life and exercise-adherence.

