Our hypothesis is that the reference intervention (Otago) is superior to the usual care (Helsana) and that the experimental intervention (T&E) is non-inferior to the reference intervention.

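### One 80% power figure is given for all study objectives, but at the protocol's own assumed rates the Otago versus Helsana test has roughly 10% to 27% power

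*Protocol article*

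**What the plan says.** The Sample size section of the protocol article links 405 participants to achieving the study objectives. Its planning figures are "power of 80%, an assumed rate of falls of 0.5 for the T&E program, 0.79 for the OTAGO and 0.92", where the last value is the Helsana rate. Type-I error is 5% overall, the margin for non-inferiority is also 5%, and dropout is taken as 15%. The arms are 162, 162 and 81, allocated 2:2:1. The section does not name the hypothesis that the 80% refers to. It also does not give the sidedness of the test, the time unit of the rates or the dispersion.

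The hypothesis at the end of the Background has two parts. The first is that "the reference intervention (Otago) is superior to the usual care (Helsana"); the second is that T&E is non-inferior to Otago.

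The Statistical analysis section sets the aim of the primary analysis: "To simultaneously demonstrate superiority of E (T&E) to R (Otago) and R (Otago) to P(Helsana"), together with non-inferiority of T&E to Otago, using negative binomial regression. The outcome is the number of falls over twelve months.

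**The concern.** Otago versus Helsana is a stated hypothesis and a named part of the primary analysis, so a reader will take the 80% to cover it. The planning figures are "0.79 for the OTAGO and 0.92 for the usual care group", a rate ratio of 0.79/0.92 = 0.859. That is a small effect, tested against the smallest arm. T&E versus Otago, by contrast, has an assumed rate ratio of 0.50/0.79 = 0.633 and two arms of 162.

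If the 80% does not extend to Otago versus Helsana, the hypothesis as written will probably not be confirmed even when every planning assumption is true. A non-significant Otago result would then say little about Otago, yet readers relying on the stated power could take it as a negative finding.

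**Working it through.** **Inputs.** From Sample size: rates 0.50, 0.79 and 0.92; arms 162/162/81; dropout 15%; overall type-I error 5%; margin 5%. From Outcomes: twelve months of follow-up. Assumptions, because the article does not state them: rates are per person-year; dispersion φ runs from 0 (Poisson, the best case) to 1; sidedness is tried both as two-sided 5% (z = 1.960) and one-sided 5% (z = 1.645); the 5% margin is a rate ratio of 1.05, or 95% retention in step 1.

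**1. Where 405 can come from.** It cannot be reproduced uniquely without the dispersion. A three-arm retention test on the rate scale with retention D = 0.95 comes close:
- Effect: 0.95×0.79 + 0.05×0.92 − 0.50 = 0.2965.
- Variance, with rate×(1+φ×rate) divided by allocation share, at φ = 0.4: 0.600/0.4 + 0.9025×1.0396/0.4 + 0.0025×1.2586/0.2 = 3.861.
- N = (1.960+0.842)² × 3.861/0.2965² ≈ 345, and 345/0.85 ≈ 406.
- At one-sided 5%, φ = 0.9 gives about 404.

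So 405 with 80% power is plausible for a T&E versus Otago test.

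**2. Otago versus Helsana.** Evaluable participants: 162×0.85 ≈ 138 and 81×0.85 ≈ 69. Log rate ratio: ln(0.92/0.79) = 0.1523. Variance = 1/(n₁r₁) + 1/(n₂r₂) + φ/n₁ + φ/n₂, and power = Φ(0.1523/SE − z).
- φ = 0: expected falls 138×0.79 = 109.0 and 69×0.92 = 63.5. SE = √(1/109.0 + 1/63.5) = 0.158, and 0.1523/SE = 0.965. Power is Φ(0.965−1.960) = 16.0% two-sided and Φ(0.965−1.645) = 24.8% one-sided.
- φ = 0.5: SE = 0.189; power 12.4% and 20.1%.
- φ = 1: SE = 0.216; power 10.5% and 17.4%.
- No dropout (162/81), φ = 0: SE = 0.146; power 18.0% and 27.4%.

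The highest of these is 27.4%. For 80% at φ = 0 and 2:2:1, the total including dropout would be about 3,420 (two-sided) or 2,700 (one-sided).

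**3. T&E versus Otago, same method, 138 per arm, φ from 1 to 0.** Non-inferiority: 74% to 91% two-sided, 83% to 95% one-sided. Superiority: 65% to 84% two-sided, 76% to 91% one-sided.

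**4. Joint power.** The two contrasts share the Otago arm, so their statistics are negatively correlated; at φ = 0 the correlation is −(1/109.0)/(0.154×0.158) = −0.38. Bivariate normal probabilities, which simulation matches to within one percentage point:

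| 138/138/69, φ from 1 to 0 | Two-sided 5% | One-sided 5% |
|---|---|---|
| Otago superior to Helsana and T&E non-inferior to Otago | 5% to 13% | 11% to 22% |
| All three results of the primary analysis | 4% to 11% | 10% to 20% |

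In the most favourable setting (162/162/81, one-sided 5%, φ = 0) these rise to about 26% and 24%.

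**The case against.** **No number has been shown to be miscalculated.** The 80% stands in a sentence that contains a non-inferiority margin, and step 1 shows that 405 fits a T&E versus Otago test. That stands. The error is one of scope: a figure that can be right for one test is presented as serving all objectives.

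**The unstated inputs could raise the power.** They can, but not enough. With rates per six months, expected counts double and power reaches 28% (two-sided, after dropout) to 43% (one-sided, no dropout), both without overdispersion. Overdispersion only lowers it.

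**The figures could be proportions of fallers.** A pooled two-proportion test with 138/69 then gives 68% two-sided and 80% one-sided. The one-sided requirement of 70 in the Helsana arm, times 1.15, gives 80.5, which rounds up to 81, the planned Helsana arm. The match is notable, but this reading conflicts with the article's own term (rate), with the negative binomial model and with the yearly faller proportion of 28–35% in the Background. If it were the origin of the size, the trial would have been sized for a different endpoint from the one it analyses.

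**Stronger readings that the document does not support.** A reader might take 16% as a ceiling; it is not, since sidedness is not stated. A reader might infer that the weak contrast blocks every T&E conclusion. The Statistical analysis section makes T&E superiority follow T&E non-inferiority, but does not make either wait for Otago to beat Helsana; the rest is left to a cited method. A reader might also call the lack of a named T&E versus Helsana test an error, given the broad objective in the Abstract ("The main objective of this study is to compare the T&E programme with the Otago Exercise Programme and the recommendation-booklet"). The stated hypothesis does not include that contrast, and the detailed procedure may be set out elsewhere.

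**Conclusion.** The point holds as a wrong scope for the power statement. With the printed rates read as per person-year, the Otago versus Helsana superiority test has about 10% to 16% power at two-sided 5% and 17% to 25% at one-sided 5% after the planned dropout, and no more than about 27% under the most favourable assumptions. The hypothesis as a whole therefore fails at least about three times in four even if all planning rates are true, and about nine times in ten at two-sided 5%.

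The result rests on a Wald test of the log rate ratio, a dispersion of 0 to 1 and one year of exposure per evaluable participant. The joint figures also depend on reading the margin as a rate ratio of 1.05. The 80% cannot be firmly assigned from the article alone: of the tests it names, only those of T&E against Otago come near that level, and whether they reach it depends on the unstated dispersion and sidedness.

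**What to change.** In Sample size:
1. Name the hypothesis that the 80% covers. On the figures shown, it can only be a T&E versus Otago test, most plausibly of the non-inferiority or retention type.
2. State the sidedness, the time unit of the rates, the scale of the 5% margin and the dispersion used.
3. In place of one 80% for all objectives, report the power that follows from those inputs for Otago versus Helsana and for the joint claim. The ranges above show what to expect; the authors should print the values from their own inputs.
4. State that a non-significant Otago versus Helsana result is not evidence against Otago.

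Placing Otago versus Helsana last in a prespecified test order, or adding T&E versus Helsana, is an optional design choice and not part of correcting the error.

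The cost is a change of wording and an amendment before unblinding, with no extra participants. The downside is that the stated power becomes less favourable.
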